## 5. Endpoints

The primary endpoint is major CIED infection during follow-up.

Major CIED infections are defined in the novel CIED infection criteria [1], resulting in [8]: CIED system removal;an invasive CIED procedure (pocket revision without removal);surgical site infection resulting in pocket revision or CIED extraction after systemic antibiotic therapy;chronic antibiotic therapy due to a major CIED infection without an invasive procedure;death.

Secondary endpoints include all-cause mortality, major CIED pocket infection, minor CIED infection, TP-related adverse device effects (ADE), CIED-procedure-related or CIED-hardware-related adverse events (e.g., pain, arrhythmia, hematoma formation that is resolved, pneumothorax that is resolved), and complications (e.g., hematoma formation requiring revision, pericardial effusion requiring drainage, pneumothorax requiring chest tube, events requiring early pocket revision) during all follow-up periods.

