## 6. Statistical Analysis

The ETPR is designed for comparisons between the intervention with TP and historical controls, with a two-sided confidence level of 0.95. The primary estimand is the rate of patients who develop a CIED infection after a CIED procedure with adjunct TP before a repeat procedure (i.e., system modification) on that CIED is performed or the patient succumbs. This rate of infection is needed to evaluate the intervention with TP during CIED placement procedures. Exact binomial statistics will be used for CIED infection rates at 3 and at 12 months, estimated as the number of procedures followed by a CIED infection relative to the number of registered procedures with at least the respective follow-up times or an event within the specified time periods. For the first sensitivity estimand, the intercurrent events (Table 2) of generator replacement, system change, revision (i.e., any procedure that touches the CIED within the follow-up period), and death are considered to be competing risks in the estimation of the cumulative incidence curve. Event times end at these events, as these events can trigger CIED infections, but sub-distribution hazards are used to calculate the cumulative incidence function. This leads to fewer upward-biased estimates than when considering these intercurrent events as censoring the event time. Censoring is restricted to failure to follow-up (i.e., death, discontinuation) and the end of observation (i.e., system modification). Other intercurrent events, such as the intravenous administration of antibiotics (e.g., in the treatment of pneumonia), will not be considered, as in the published intention-to-treat data. Their sum is expected to be independent of TP use. This decision is taken to avoid estimates that are too low for the evaluation of the intervention.

Another objective is to gather planning data for future studies. In randomised controlled trials (RCT), the primary estimand is the cause-specific hazard ratio. This translates into censoring at the occurrence of competing risks. The second sensitivity estimand of the ETPR is the rate of major CIED infections per time survived without competing risks. 

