The confidence level will not be adjusted for multiple checks, as all analyses will be performed, and conclusions will be based on the latest results of the interim analyses or final results only. Times to major CIED infection or to death will be analysed using Kaplan–Meyer curves and cause-specific hazard ratios for the numbers of risk factors related to the patient, the CIED, or the procedure. ADE and complications will be analysed similarly using logistic regression.

The secondary estimand is all-cause mortality after CIED procedures using TP between procedures accessing the pocket. Intercurrent events are handled similarly (see Table S1 in the online supplement).

To facilitate causal inference in future research, the known risk factors for major CIED infection are reported. Their distribution should enable the calculation of propensity scores or more general balancing weights [31]. Such analyses would consider the randomness of historic controls instead of using historic results as performance goals.

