### Sample Size

The performance goals for the rate of major CIED infections vary according to country, evidence level, CIED type, and patient selection. They are expected to be higher in a revision procedure involving a complex CIED in high-risk patients than for de novo implants in otherwise healthy patients within a well-maintained setting. Additionally, the novel criteria for major CIED infection have evolved [1]. Accordingly, the published 12-month rates range from 0.7% to 4.2% (Table 3). The three-month rates are available from WRAP-IT and the Danish device registry, with values of 0.8% and 1.0% in controls, respectively [32]. For future studies researching TP use, we expect to plan for a 12-month rate of 0.5%. If its ratio to the three-month rate is 0.8/1.2, as in the WRAP-IT controls [8], then we assume a three-month rate of 0.33%.

For an approximate 95% confidence interval, to exclude a risk difference of 0.8% − 0.33% = 0.47%, when the true event rate is 0.33%, the sample size needs to exceed 572. 

For an exact 5% binomial test to have a power of 80% in detecting the difference between the hypothetical rate of 1% (0.8%) and the true rate of 0.33%, the sample size needs to be 1140 (2000).

Assuming a major CIED infection rate in the registry of 0.5% at 12 months and 0.33% at 3 months, a comparison with the performance criteria from the literature would require the sample sizes shown in Table 3.

We therefore plan to publish the ETPR results after the twelve-month follow up of 400, 900, 1420, and 2300 procedures. For the long-term evaluation, a report after the follow-up period of 36 months is planned for all procedures enrolled.

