## 8. Conclusions

Recently, we have learned about the practice whereby the majority of centres use irrigation solutions containing various antimicrobial substances in everyday practice in the hope of gaining the advantage in the battle against localised CIED infections [38]. However, high-quality evidence to support these measures is missing or not supportive [7,39].

The solution researched in the ETPR is the use of an adjunct during CIED placement. It has been designed to keep all CIED system components disinfected during any invasive CIED procedure. It is certified in this context. The ETPR will be fit to provide information regarding efficacy while researching the safety of the intervention with TP during CIED placement, both for the patients and the CIEDs. Eventually, the ETPR will serve as a collection of complications related to the placement of CIEDs during a maximum follow-up period of 36 months.

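### Logistic regression is assigned to ADE and complications over follow-up of up to 36 months, with no time window and no rule for procedures observed for less time

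*Protocol article*

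**What the plan says.** Protocol article, 6. Statistical Analysis, gives one method for infection and death by number of risk factors: "Times to major CIED infection or to death will be analysed using Kaplan–Meyer curves and cause-specific hazard ratios". The next sentence reads: "ADE and complications will be analysed similarly using logistic regression". It names no time point, denominator or exposure term.

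Section 5, Endpoints, lists ADE, procedure- or hardware-related adverse events and complications as secondary endpoints. The list ends "events requiring early pocket revision) during all follow-up periods". Section 8 adds that "the ETPR will serve as a collection of complications related to the placement of CIEDs during a maximum follow-up period of 36 months".

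The Sample Size section sets the reporting dates: "We therefore plan to publish the ETPR results after the twelve-month follow up of 400, 900, 1420, and 2300 procedures". For the long term, "a report after the follow-up period of 36 months is planned for all procedures enrolled".

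Section 6 also says that observation can end through death, discontinuation or system modification. For infection rates at 3 and 12 months, it counts events "relative to the number of registered procedures with at least the respective follow-up times or an event within the specified time periods".

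**The concern.** Logistic regression has no time axis. It suits an outcome that is known for every procedure at a common horizon. Here the outcome is defined over follow-up of up to 36 months, and procedures are not all observed for equally long, for two reasons:

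- **Staggered entry.** Recruitment is consecutive over several years. When the last procedure in one of the four reports reaches 12 months, earlier ones may have been followed for longer. The text does not say that only the first 12 months will be used.
- **Early end.** Death, discontinuation and system modification shorten observation at every report, including the 36-month one.

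The article handles this for infection, with a completeness denominator, a competing-risk analysis and a rate per time survived. It does not clearly carry any of these over to ADE and complications. The word *similarly* could be read either way.

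The registry aims to understand the factors that drive complications (Section 3), to reveal possible late effects (Section 2) and to compare adverse events with the literature (Section 7). A proportion tied to no time point serves these aims poorly and can shift from report to report as follow-up matures.

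**Working it through.** **The plan's own figure.** None is given for this analysis, so there is nothing to reproduce. The check asks how far the answer depends on the missing counting rule.

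**Inputs.** From the documents: the 36-month horizon, the reporting dates, the causes of early end and the completeness denominator. Assumed, because the documents give no values: a binary risk factor with 50% prevalence and hazard ratio 2; risk in the unexposed in months 0–3 (e) and months 3–36 (l); and the pattern of follow-up. Each scenario was simulated with 2 million procedures.

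**Formulas.** With m = 1 (unexposed) or 2 (exposed), and G(t) the chance of still being under observation at t:

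- True 36-month risk: R = 1 − [(1 − e)(1 − l)]^m
- All procedures counted, unobserved time scored as event-free: A = ∫ f(t)G(t)dt, where f is the density of the event time
- Completeness denominator: B = A / [A + (1 − R)G(36)]

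**Worked case: mostly late events, e = 0.5%, l = 5%; 10% (unexposed) and 30% (exposed) lost by 36 months.**

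- Unexposed: R = 1 − 0.995 × 0.95 = 5.5%; A = 5.2%; B = 0.0520/(0.0520 + 0.9453 × 0.90) = 5.8%.
- Exposed: R = 1 − 0.94525² = 10.7%; A = 9.0%; B = 0.0900/(0.0900 + 0.8935 × 0.70) = 12.6%.
- Odds ratios by this direct calculation: 2.06 true, 1.80 under A, 2.35 under B. The simulation gave 2.06, 1.79 and 2.34.

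**Simulated results, 36-month window**

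| Scenario | Risk: true / A / B | Odds ratio: true / A / B |
|---|---|---|
| Late events (0.5% + 5%), loss 30% vs 10% | 8.0% / 7.1% / 8.7% | 2.06 / 1.79 / 2.34 |
| Mostly early (8% + 2%), loss 30% vs 10% | 14.3% / 13.8% / 16.7% | 2.11 / 2.03 / 2.63 |
| Rare, mostly late (0.45% + 1.65%), follow-up uniform over 12–36 months | 3.1% / 2.2% / – | 2.03 / 2.00 / – |
| Mostly early (8% + 2%), follow-up uniform over 12–36 months | 14.3% / 13.4% / – | 2.12 / 2.11 / – |
| Late events (0.5% + 5%), exposed followed to 36 months, others 12–36 | 8.1% / 7.2% / – | 2.06 / 3.09 / – |

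B is not usable in the last three rows, because almost no event-free procedure in a staggered group has a full 36 months. With follow-up uniform over 12–36 months, the 3- and 12-month windows show no bias.

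**What the early ends are matters.** In the first two rows, the true risk is the right target if the early ends are loss to follow-up. If they are deaths or unrelated revisions, A is itself the 36-month cumulative incidence. A is then correct and only B is wrong: in the first row, 8.7% against 7.1%.

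**Check on attenuation.** Take event hazards h of 0.03 and 0.06 per year, which give 36-month risks of 8.6% and 16.5% without early end (odds ratio 2.09). Let early end occur at rates c of 0.05 and 0.20 per year, all of it competing events. The cumulative incidence is h/(h + c) × [1 − exp(−3(h + c))]:

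- Low risk: 0.03/0.08 × (1 − e^−0.24) = 8.0%
- High risk: 0.06/0.26 × (1 − e^−0.78) = 12.5%
- Odds ratio: (0.125/0.875)/(0.080/0.920) = 1.64

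Pooling follow-up over 12–36 months with the same rates gives 5.5% and 9.1%, odds ratio 1.74. Both risks are too low, but the odds ratio is not attenuated against 1.64. It is attenuated only against 2.09. With early end at 5% per year in both groups, the pooled odds ratio is 2.06, practically unchanged from 2.09.

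**The case against.** A reader might infer that the plan treats every procedure as fully observed, and so understates late risks and risk-factor effects. The documents do not support that. Nowhere does the article say that unobserved time is scored as event-free. Its only stated rule for a binary outcome is the completeness denominator, which pushes risks and odds ratios the other way. Staggered entry is also limited: the 36-month report waits for all procedures, and observation below 12 months at the earlier reports comes from early end, not late entry. The direction for odds ratios depends on whether the risk factor is related to length of observation, and on the target chosen.

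It can also be said that most of the complications named in Section 5 (pneumothorax, pericardial effusion, hematoma, early pocket revision) are peri-procedural. Logistic regression is reasonable for these, and the effect on them is small if all procedures are counted. This stands, although the completeness denominator would still distort a 36-month result (14.3% to 16.7%).

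Finally, windows and denominators for a secondary analysis are often left to an analysis plan or full protocol, and neither is shown. The plural in Section 5 is compatible with separate 3-, 12- and 36-month windows. This lowers the weight of the point but does not remove it, because the article itself chooses a method without a time axis for an endpoint that it defines over long follow-up. The supplementary table of intercurrent events is cited for the mortality estimand, not for this one.

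**Conclusion.** The point holds as a mismatch between the stated method and the period over which ADE and complications are counted. For events after the early period, the estimate depends on how procedures with shorter observation are counted:

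- **Risks** are too low if unobserved time is scored as event-free. This arises mainly when unequal follow-up is pooled in the four 12-month-triggered reports, or through loss to follow-up. They are too high if the completeness denominator is carried over and drops deaths and revisions.
- **Risk-factor odds ratios** may be unchanged, attenuated or inflated. No general direction can be claimed.

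Under the assumed inputs, the all-counted 36-month risk falls short by between 0.5 of 14.3 percentage points (mostly early events, loss only) and 0.9 of 3.1 (rare late events, staggered follow-up). These sizes rest on assumed event timing and loss rates and cannot be fixed from the documents. The matter concerns secondary endpoints and should be corrected, but it does not touch the primary infection analysis.

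**What to change.** Replace the sentence with two rules.

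1. Keep logistic regression for procedural complications within a fixed early window (discharge or 3 months), observed for nearly all procedures.
2. For ADE, hardware-related events and complications over longer follow-up, analyse time to first event. Report cumulative incidence at 3, 12 and 36 months and cause-specific hazard ratios for the number of risk factors. Treat death and re-intervention for other reasons as competing events, and censor loss to follow-up. A re-intervention that itself defines the complication, such as a hematoma requiring revision, counts as the event and not as a competing one.

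The cost is a few lines of text. Last-observation dates are already needed for the infection analysis. The downside is that onset dates must be derived for adverse events, and events noticed only at a visit will have approximate dates.

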### Sample Size

The performance goals for the rate of major CIED infections vary according to country, evidence level, CIED type, and patient selection. They are expected to be higher in a revision procedure involving a complex CIED in high-risk patients than for de novo implants in otherwise healthy patients within a well-maintained setting. Additionally, the novel criteria for major CIED infection have evolved [1]. Accordingly, the published 12-month rates range from 0.7% to 4.2% (Table 3). The three-month rates are available from WRAP-IT and the Danish device registry, with values of 0.8% and 1.0% in controls, respectively [32]. For future studies researching TP use, we expect to plan for a 12-month rate of 0.5%. If its ratio to the three-month rate is 0.8/1.2, as in the WRAP-IT controls [8], then we assume a three-month rate of 0.33%.

For an approximate 95% confidence interval, to exclude a risk difference of 0.8% − 0.33% = 0.47%, when the true event rate is 0.33%, the sample size needs to exceed 572. 

For an exact 5% binomial test to have a power of 80% in detecting the difference between the hypothetical rate of 1% (0.8%) and the true rate of 0.33%, the sample size needs to be 1140 (2000).

Assuming a major CIED infection rate in the registry of 0.5% at 12 months and 0.33% at 3 months, a comparison with the performance criteria from the literature would require the sample sizes shown in Table 3.

We therefore plan to publish the ETPR results after the twelve-month follow up of 400, 900, 1420, and 2300 procedures. For the long-term evaluation, a report after the follow-up period of 36 months is planned for all procedures enrolled.

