## Figures and Tables

**Figure 1 mps-06-00086-f001:**
[figure not shown]
Enrolment and follow-up of ETPR participants; CIED denotes cardiac implantable electronic device.

**Table 1 mps-06-00086-t001:** Follow-Up Schedule.

Post-Procedure Visits	De Novo (Including Lead Only in Upgrade or Downgrade)	Box Exchange
Hospital discharge	**X**	**X**
1 month	X	
3 months	**X**	**X**
12 months	**X**	**X**
24 months	**X**	**X**
36 months	**X**	**X**

X, clinical routine; **X**, registry follow-up recorded.

**Table 2 mps-06-00086-t002:** Intercurrent events, their handling in the analysis for the first sensitivity estimand, and the rationale. The prevented bias is the bias that would have been incurred without action. The possible bias is a bias that may be incurred by the action. CI = confidence interval, MNAR = missing not at random, MAR = missing at random.

Intercurrent Event	Prevented Bias	Action	Analysis Strategy	Missingness Assumed	Possible Bias
Other or no disinfectant	Upward	No follow-up	Principle stratum	MNAR	Downward
No permanent implantation	Downward	No follow-up	Principle stratum	MNAR	Upward
Conversion to open surgery	Upward	Full follow-up	Treatment policy	--	Upward
Antibiosis for infections not related to CIED	?	Full follow-up	Treatment policy	--	?
Pocket hematoma, septic thrombophlebitis	?	Full follow-up	Treatment policy	--	?
Minor CIED infection	?	Full follow-up	Treatment policy	--	?
Box exchange	Upward	Competing risk	Hybrid	MNAR	Wide CI
System modification	Upward	Competing risk	Hybrid	MNAR	Wide CI
Other intervention touching the CIED pocket	Upward	Competing risk	Hybrid	MNAR	Wide CI
Death	Upward	Competing risk	Hybrid	MNAR	Wide CI
Lost to follow-up for another reason	Upward, narrow CI	Censoring	Treatment policy	MAR	Wide CI

**Table 3 mps-06-00086-t003:** Historic major CIED infection rates and sample sizes N needed to demonstrate superiority over such external fixed performance goals, if the true new rate is 0.5% at 12 months or 0.33% at 3 months. Sample sizes in bold are selected to issue registry reports.

Source	Follow Up (Months)	Historic CIED Infection Rate (Literature)	Hypothetical CIED Infection Rate (ETPR)	N for Approximate 95% Confidence Interval	N for Exact Test with Power 80%
WRAP-IT [8] verum	3	0.45%	0.33%		
WRAP-IT [8] verum	12	0.7%	0.50%	4778	12200
WRAP-IT [8] control	3	0.80%	0.33%	**572**	2000
WRAP-IT [8] control	12	1.2%	0.50%	**391**	**1420**
PADIT [7]	12	1.03%	0.50%	**681**	**2300**
Henrikson [33]	3	1.0%	0.33%	282	1140

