Danish registry [32]	6?	1.43%	0.50%	221	**880**
FLUSH-IT control	12	2.4%	0.50%	53	330
US insurance [9]	NR	4.2%	0.50%	14	101
Polyzos low [34]	NR	1.0%	0.33%	282	1140
Polyzos low [34]	NR	1.0%	0.50%	765	2370
Polyzos high [34]	NR	1.3%	0.33%	135	608
Polyzos high [34]	NR	1.3%	0.50%	299	1050

NR = not reported.

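### The fixed historical goals are not shown to count the same infections as the registry endpoint, so a difference in definition could pass for a TP effect or hide one

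*Protocol article*

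**What the plan says.** Section 5 (Endpoints) defines the primary endpoint by two conditions that must both hold: "Major CIED infections are defined in the novel CIED infection criteria [1], resulting in [8]: CIED system removal", followed by further consequences (an invasive procedure without removal, revision or extraction after systemic antibiotics, chronic antibiotics, death). Reference [8] is WRAP-IT, as Table 3 shows.

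Section 6 (Statistical Analysis) sets the comparison: "The ETPR is designed for comparisons between the intervention with TP and historical controls, with a two-sided confidence level of 0.95". The caption of Table 3 describes its entries as "sample sizes N needed to demonstrate superiority over such external fixed performance goals". The planning rates are fixed in the Sample Size section: "Assuming a major CIED infection rate in the registry of 0.5% at 12 months and 0.33% at 3 months".

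That section says that performance goals vary with country, evidence level, CIED type and patient selection. It then adds: "Additionally, the novel criteria for major CIED infection have evolved [1". It presents the range of published 12-month rates, 0.7% to 4.2%, as following from these points. Table 3 carries the published rates over as they stand. Its bold sample sizes, selected for reports, belong to WRAP-IT control (1.2% at 12 months, 391 and 1420; 0.80% at 3 months, 572), PADIT (1.03%, 681 and 2300) and the Danish registry (1.43%, 880, follow-up entered as 6 with a question mark). Reports are planned at 400, 900, 1420 and 2300 procedures.

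**The concern.** A single-arm rate can be set against a fixed external rate only if both count the same events over the same time. Here the article names a change in infection criteria as a reason why published rates differ. It then states no source's event definition, does not limit the goals to sources with a matching definition, and does not plan to recount registry events under a source's definition. If the registry definition counts fewer events than a source did, the registry rate will lie below the goal even when TP has no effect. If it counts more, a real effect may be missed.

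The balancing weights mentioned in Section 6 cannot repair this. They act on patient and procedure risk factors, not on what is counted as an event, and they are left to future research. The limitations in Section 7 cover patient selection and centre differences but not outcome definition.

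The Discussion illustrates the preventive effect of TP by comparing registry rates with the literature. The observed rate is also meant to feed sample-size planning for later randomised trials, so an unrecognised shift would carry over into them.

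**Working it through.** **1. The plan's own figures.** The confidence-interval column of Table 3 follows N = 1.96² · p1(1 − p1) / (p0 − p1)², where p0 is the goal and p1 the assumed registry rate.

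- WRAP-IT control, 3 months: 3.8415 × 0.0033 × 0.9967 / 0.0047² = 572.0 (stated 572).
- WRAP-IT control, 12 months: 3.8415 × 0.005 × 0.995 / 0.007² = 390.0 (stated 391).
- PADIT: 3.8415 × 0.005 × 0.995 / 0.0053² = 680.4 (stated 681).

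For the exact test, take the largest count c with P(X ≤ c | n, p0) ≤ 0.025, which is the lower half of a two-sided 5% test. Power is P(X ≤ c | n, p1).

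- n = 1420, p0 = 1.2%: c = 9, power 82.1%. This is the first n to reach 80%.
- n = 2300, p0 = 1.03%: c = 14, lower tail 2.2%, power 81.6%.
- n = 900, p0 = 1.43%: c = 5, lower tail 1.1%.

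The sizes 1420 and 2300 are thus reproduced, and the goals enter as fixed constants.

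**2. How few events decide the result.** At the assumed 0.5%, the expected counts are:

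- 1420 × 0.005 = 7.1 against a limit of 9;
- 2300 × 0.005 = 11.5 against a limit of 14;
- 900 × 0.005 = 4.5 against a limit of 5.

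Three additional events take the first two past their limits (10.1 and 14.5). One takes the third past its limit (5.5).

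**3. Effect of a definition shift alone.** Let r be the ratio of events counted under the registry definition to events counted under the source's definition, in the same patients. With no TP effect the registry rate is r · p0, and the chance of declaring superiority is P(X ≤ c | n, r · p0). The documents give no rate under both definitions, so r is an assumption and is shown as a range.

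| r | PADIT 1.03%, n = 2300 | WRAP-IT control 1.2%, n = 1420 | Danish registry 1.43%, n = 900 |
|---|---|---|---|
| 1.1 | 0.7% | 1.0% | 0.5% |
| 1.0 | 2.2% | 2.5% | 1.1% |
| 0.9 | 6.2% | 5.9% | 2.6% |
| 0.8 | 15.1% | 12.7% | 5.6% |
| 0.7 | 31.5% | 24.8% | 11.4% |

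**4. Where the definitions can differ.**

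- *WRAP-IT control:* the consequence list in Section 5 is cited to this trial. On the face of the article only the layer from [1] can differ.
- *PADIT and the Danish registry:* nothing in the article ties either rate to the criteria in [1] or to the consequence list. For the Danish registry the follow-up time is also uncertain, while Table 3 pairs its rate with 0.50%, the assumed 12-month rate. If its rate covers a shorter time than the registry count, that mismatch works against TP.

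**The case against.** Several points on the other side are sound.

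- **WRAP-IT is the best-aligned goal.** A reader might infer that the consequence list sets the registry apart from every comparator. The citation to [8] speaks against that for the goal behind the 1420 report, so the middle column of the table is the least likely to apply.
- **The direction is not established.** A reader might infer that requiring a consequence makes the registry definition narrower and so flatters TP. That is plausible, but the article reproduces neither the criteria in [1] nor any source's definition. At r = 1.1 the test becomes conservative.
- **The timing of the change is not stated.** The article says that the criteria have evolved. It does not say that they changed after a particular goal was published.
- **The weakest rows set no report size.** The US insurance rate (4.2%) and the rates from source [34], all with follow-up not reported, are not bold. They remain in a table of superiority goals, but the reports do not rest on them.
- **The antibiotic item is not a real circularity.** The phrase "chronic antibiotic therapy due to a major CIED infection without an invasive procedure" reads naturally as referring back to infection as defined by [1]. It is loose wording at most.
- **Some of what falls outside the primary count may still be recorded.** Minor CIED infection is a secondary endpoint, and Section 5.1 gives every suspected infection a defined work-up.

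It can also be said that a condensed article leaves comparator definitions to the full protocol, and that the stated aim is planning data. The first would excuse a missing table of definitions. It does not excuse a method that, as written here, tests one endpoint against goals of unstated definition, because the article itself fixes the goals, the test and the report sizes. The second does not help, because a planning rate also depends on what was counted.

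**Conclusion.** The concern stands in limited form. The superiority comparisons assume that registry and goals count the same events. The article itself gives a reason to doubt this and provides no step to check it. The doubt is greatest for the PADIT goal (report at 2300) and the Danish registry goal (N 880, presumably rounded up to the report at 900). It is smaller for WRAP-IT control.

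Over the assumed range of r from 1.1 to 0.7, the chance of declaring superiority without any TP effect runs from 0.7% to 31.5% at n = 2300 against 1.03%, and from 1.0% to 24.8% at n = 1420 against 1.2%. These figures show sensitivity. They rest on an exact lower-tail test at 2.5%, on goals taken as fixed and on hypothetical values of r. They are no evidence that a shift of any given size exists or that it favours TP. The point deserves a change to the analysis method, because few events decide each report and the remedy is cheap.

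**What to change.** 1. In Section 6, state the source's event definition and follow-up time for each goal used in a superiority comparison, at least for the bold rows (WRAP-IT control, PADIT, Danish registry).
2. Classify each suspected registry infection under that source's definition as well as under the registry definition, using the work-up data already collected under Section 5.1.
3. Compare each goal only with the registry rate under the matching definition and follow-up. Keep the rate under the registry's own definition as the descriptive primary result.
4. Show any goal whose definition or follow-up cannot be reproduced from registry data as context, without a superiority claim.
5. Add differences in outcome definition to the limitations in Section 7.

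The cost is a small amount of recoding. The documents do not give the number of suspected infections. Major infections at 2300 procedures would number about 12 at 0.5% (11.5) and about 24 at the PADIT rate (2300 × 0.0103 = 23.7). The downside is that some rows of Table 3 may stop serving as superiority goals. If a bold row is among them, the report size based on it needs a new justification.
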